**Fig. 2 Fig2:**
[figure not shown]
Cluster RCT of the Comprehensive School Safety Intervention delivered using the implementation facilitation strategy

### Study setting

The current study is in Genesee County, Michigan. Widespread losses in industrial jobs in many US cities have led to unemployment, population loss and changes in land use (including high rates of vacant buildings); these demographic and economic changes have contributed to neighborhood instability, disadvantage and elevated rates of violent crime (Glaeser & Gyourko, 2005; Sampson, Raudenbush, & Earls, 1997). Genesee County, especially around the city of Flint, has lost almost 90% of the automotive industry jobs that bolstered its economy in the 1960s. The economic hub of Genesee county, Flint’s current challenges include high rates of poverty (60% of children live in poverty) (U.S. Census Bureau, 2015) and an unemployment rate that is 50% higher than the state average (Bureau of Labor Statistics, 2014). Across Flint community elementary schools, 92% of students are eligible for free or reduced lunches (Michigan Department of Education, 2017). Surrounding Genesee communities face similar disadvantage with poverty (see Table 1) and violence rates exceeding state averages. This high level of community violence has significant implications for levels of trauma and corresponding mental health issues for youth residing in Flint and surrounding Genesee County.

**Table 1 Tab1:** Study Sites by demographic variables

School	Free or Reduced Lunch ^a^	Grade 3–8 Students proficient in Math and English (2017–2018)^b^	Racial/ethnic minority composition^a^
1	78%	7.6%	34%
2	86%	38.6%	31%
3	55%	15.0%	29%
4	66%	26.3%	12%
5	91%	3.4%	73%
6	76%	9.9%	16%
7	84%	10.4%	24%
8	84%	2.5%	86%
9	78%	12.9%	69%
10	55%	29.4%	31%
11	97%	14.6%	100%
12	75%	32.0%	72%
13	91%	6.4%	72%
14	68%	34.1%	40%
15	84%	15.0%	74%
16	66%	29.5%	21%
17	56%	16.9%	10%
18	52%	27.1%	96%
19	95%	3.2%	9%
20	90%	11.1%	93%
State of Michigan	45.9%	30.7%	67.0%

^a^Data provided by the partner intermediate school district, internal data

^b^Parent Dashboard for School Transparency, Center for Educational Performance and Information, https://www.mischooldata.org Accessed 9/13/2019

### School safety challenges

School safety is a major concern in Flint and Genesee Co. as a whole. In a survey of Genesee Co. 4th through 6th grade students, 42% reported seeing violence in the school once per month or more, 13% did not feel safe while at school, and 3% skipped school because they were afraid of being hurt. There were also widespread mental health challenges: 44% of students worried a lot, 43% felt nervous, 30% could not stop being sad, and more than half felt they were too tired to do things (Prevention Research Center of Michigan, 2011).

### Study design

See Fig. 2 for study flow diagram. In the pre-implementation phase, the project team will meet with intermediate school partners and individual schools, finalize processes and measures, secure formal agreements of study participation with schools, hire staff for the project and schedule all trainings. The current study is a cluster randomized trial in which each school will participate in the study over two years. The interventions will be staggered (5 intervention + 5 control schools starting in Year 1; 5 additional intervention and 5 additional control schools in Year 2) in order to maximize the likelihood of intensive implementation. It focuses on three key areas: (i) at a universal prevention level, focusing on changes to the physical school environment (CPTED) and promoting consistent and fair discipline and reward practices (RJ); (ii) a more targeted approach, to help those with early signs of mental health problems (MHFA); and (iii) engaging those involved in violent or aggressive situations at school through RJ practices. As noted above, the interventions are guided by a 3-PLT who seek to utilize the interventions to promote positive school climate.

### Sample

#### Schools

We will recruit 20 schools and implement the intervention across three school years (see Table 1). Co-educational elementary schools in Genesee County Intermediate School District (GISD), Michigan will be invited to participate. Schools participating will be similar in terms of proportion of students receiving free/reduced school lunches and approximate size of the school. Prior to the intervention roll-out, all 20 schools will be randomized to intervention or control. The intervention will be implemented in stages. Cohort 1 schools will include 5 intervention and 5 control schools. Cohort 2 will include10 additional schools (5 intervention and 5 control) for a total of 10 intervention and 10 control schools; each school will implement the intervention for two years.

#### Student eligibility and recruitment

There are 21 public school districts and 13 academies (charter schools) serving over 67,000 students in the GISD. Recruitment efforts will begin with presentations to the superintendents of the schools and academies. This will be followed up by similar presentations and briefings to school building principals and/or their designees (dean of students, academic services, teachers). The briefings explain the goals of the research project, the benefits to participating schools, anticipated intervention and research activities, eligibility, and similar issues. Eligibility includes having at least two grades between grades 4–6 and having a student population with 50% or higher free or reduced school lunch eligibility, being involved in MIBLISI (Michigan’s Integrated Behavior and Learning Support Initiative) and PBIS (Positive Behavioral Interventions & Supports) and being committed to the project. Across Genesee County, there are currently an average of 180 4th–6th graders in each school resulting in a maximum sample size of 3600 students over the course of the study (using a 66% consent/retention rate).

### Evidence-based interventions to be implemented

#### Universal and targeted prevention

*Universal strategies* address an entire population regardless of risk level or current behavior. This approach aims to reach a large number of individuals at once; it develops strategies and a supportive environment that enables all children to achieve sufficient competence to thrive, and thus prevent or reduce engagement in violence (Leshner, 1997). In contrast, *targeted strategies* are designed for individuals who meet specified risk criteria, for example, showing signs of mental illness (Leshner, 1997). Simultaneous deployment, particularly one tailored to a school’s culture, is commonly considered more likely to effect change (Bonell et al., 2010; Maddox & Prinz, 2003). The proposed intervention incorporates universal and targeted approaches facilitated by a school-based 3-PLT. The team will participate in ongoing activities and engagement with school staff and students to support and reinforce the interventions, foster school-community relationships and support sustainability. These activities will be led by the CS who will apply principles of implementation facilitation to promote effective EBI delivery and tailor the interventions to the context.

The universal and targeted prevention design reflects the integrated and comprehensive intervention and suggested best practice, i.e. is comprehensive, improves access to mental health, balances physical and psychological safety, employs a positive school discipline approach, considers and responds to each schools’ culture and context, and acknowledges that change takes time (PriCowan et al., 2013). Prior school safety interventions have tended to implement these strategies in isolation rather than integrating in a coordinated manner. The proposed research will advance comprehensive school safety and using of implementation science to enhance delivery of such programs.

#### Restorative justice (RJ)

Restorative justice is a philosophy and process that defines crime as doing harm to people and relationships, rather than simply violating the law (Zehr, 2002). Thus, it requires consideration of the victim and community during the justice process. Although the definition continues to evolve, it has most commonly been described as “a process whereby all the parties with a stake in a particular offense come together to resolve collectively how to deal with the aftermath of the offense and its implications for the future” (Marshall, 1996). Restorative practices focus on repairing the harm caused, engaging victims and relevant school community members in the decision making process, holding offenders accountable, and preventing similar actions in the future. By focusing on accountability, fairness, and situational responses to unique events, restorative justice provides a useful framework for alternatives to zero tolerance or traditional disciplinary actions for school violence. Overall, researchers have found robust support for RJ practices, including enhanced school safety, reduced discipline problems and other behavioral referrals (Karp & Breslin, 2001; Mirsky, 2011; Stinchcomb, Bazemore, & Riestenberg, 2006).

Prior research suggests that RJ practices may have particular efficacy for youth in the age ranges targeted in this project. Researchers found, among students 14 years and younger, that youths participating in family group conferences were less likely to re-offend than youths participating in other court-ordered programs (McGarrell & Hipple, 2007). Further, offending youths, parents, and victims all expressed much more favorable perceptions of the fairness, respect, and value of the conference experience (McGarrell, 2001). Long-term follow-up of this research demonstrated that conferences following principles of “restorativeness” and “procedural fairness” were associated with reduced re-offending at 24 months and 10 years following the original conference (Hipple, Gruenewald, & McGarrell, 2014, 2015).

Restorative justice programs can be implemented in a variety of ways to meet the needs of individual schools, but retain a set of common principles: (1) repair harm, (2) reduce risk, and (3) empower community (O’Brien, 2007). When applied to school environments, the restorative approach comprises an overarching philosophy and processes that build community in classrooms and entire schools and include proactive processes that aim to prevent wrongdoing (Mirsky, 2011). This may be accomplished through school-wide discipline practices promoting fairness in rules and enforcement, as well as consistency of reinforcing positive behavior, and may include more targeted approaches like peer mediation (Bazemore & Umbreit, 2004; Reimer, 2011). Peer mediation involves a facilitated discussion with multiple stakeholders including the offender, victims, family members, friends, school personnel, and community members. It is typically used in response to a specific offense, to explore what happened, address and repair the harm done, and determine strategies for preventing it in the future. The 3-PLT and particularly the mental health expert will lead many of the proposed peer mediation and restorative justice components of the program and it aligns closely with the support in the MHFA and climate change associated with CPTED. Within this framework, individual schools can tailor the approach as needed for their school and more specifically for each mediation need.

#### Mental health first aid (MHFA)

MHFA is defined as help provided in the context of a mental health problem or mental health crisis; importantly, the help is provided until appropriate professional help is received or the crisis is resolved (Yap & Jorm, 2011). The Substance Abuse and Mental Health Services Administration (SAMSHA) (SAMHSA National Registry of Evidence-based Programs and Practices, n.d.) lists MHFA as part of its National Registry of Evidence-based Programs and Practices. Trainers deliver an 8-h session not intended to teach therapeutic skills but rather to raise awareness of mental illness symptoms and build skills in providing initial help and guiding someone toward treatment (Kitchener & Jorm, 2006). It includes highlighting evidence-supported treatment and engaging individual resources (e.g., family).

Qualitative studies and randomized controlled trials of MHFA indicate greater confidence to help, less stigma around mental illness, better recognition of symptoms, and improved perceived value (Jorm, Blewitt, Griffiths, Kitchener, & Parslow, 2005; Jorm, Morgan, & Wright, 2008; Kelly et al., 2011; Yap & Jorm, 2011, 2012; Yap, Wright, & Jorm, 2011). Research examining MHFA has focused on adults and adolescents, yet preadolescents are also in need of timely and appropriate mental health services, suggesting value in evaluating and validating an extension of the approach for preadolescents.

Teachers are typically not trained in mental health (Reinke, Stormont, Herman, Puri, & Goel, 2011) but are in a position to identify early symptoms, which if managed promptly can substantially reduce negative outcomes and healthcare costs (Knapp, McDaid, & Parsonage, 2011). MHFA training may support teacher needs by providing resources and skills as well as debunking misconceptions and myths which may otherwise reduce helping behavior (Yap & Jorm, 2011). Teachers typically do not feel prepared to identify or manage mental health concerns (Koller, Osterlind, Paris, & Weston, 2004), yet mental health issues among children and youth is on the rise (Fombonne, 1998). Among elementary school teachers, 91% indicated they were concerned about a student’s family stressors, 76% about anxiety, and 54% about depression; 94% also agreed that schools should be involved in addressing mental health issues. Further, teachers’ beliefs that they could help students depended on their own positive psychological wellbeing, satisfaction with school climate, and confidence (Sisask et al., 2014), highlighting further potential benefits of MHFA through promoting close relationships with community mental health and a positive school climate. The current study seeks to train all school staff to provide MHFA; the climate specialists will conduct periodic MHFA ‘boosters,’ and serve as a resource to teachers and students.

#### Environmental design

The CDC (Centers for Disease Control and Prevention (CDC), 2019) identifies environmental design as an area of interest for school violence prevention, with an ongoing study of Crime Prevention Through Environmental Design (CPTED). There are typically six components: surveillance, territoriality, image/management, access control, activity support, and target hardening (Cozens, Saville, & Hillier, 2005). *Surveillance* may be natural (e.g., teachers’ office overlooking the playground), formal (e.g., playground duty or police patrols), or mechanical (e.g., cameras). *Image/management* refers to maintaining or improving physical spaces (e.g., graffiti cleanup). *Territoriality* refers to promoting a “sense of ownership” by legitimate users, thus reducing the likelihood of “illegitimate” use. *Access control* limits the accessibility of potential targets. *Activity support* promotes “intended patterns” of use for public spaces (e.g., increasing pedestrian traffic). Finally, *target hardening* increases offender effort (e.g., by installing fences). Such elements may be differently considered as they best relate to promoting positive school climate in each school. In consultation with environmental design experts, school staff, and student input, the 3-PLT will work to implement actionable design changes to improve feelings of safety, beautification, ownership, and youth empowerment.

#### Surveillance

Cameras have become increasingly prevalent^3^ and are the second most common security measure (77% of schools), after locking/monitoring doors during school hours (93%) (Gray & Lewis, n.d.). While many school administrators believe cameras to be effective (Garcia, 2003), there is little evidence to suggest students share their confidence (Bracy, 2011; Brown, 2006). Cameras do not significantly reduce students’ self-reported victimization (Blosnich & Bossarte, 2011); rather, they may be associated with increased likelihood of physical victimization (Jeong, Kwak, Moon, & San Miguel, 2013) and fear of harm (Bachman, Randolph, & Brown, 2011). Other security measures (e.g., guards, metal detectors, locker checks) may increase fear of crime (Schreck & Miller, 2003). These highly visible efforts may increase fear by signaling the school must be unsafe (Schreck & Miller, 2003) or, “coercive” measures may contribute to an “atmosphere of mistrust (Brown, 2006).” As a whole, evidence suggests that such measures may not be particularly effective in increasing school safety; by contrast, other CPTED components such as territoriality or image/management remain more promising.

#### Image/management

Though the impact of school physical environment on safety remains relatively understudied (Johnson, 2009), evidence suggests it has merit. Wilcox et al. (Wilcox, Augustine, & Clayton, 2006) found that school disorder (e.g., presence of graffiti, litter) had a significant positive association with teachers’ perceptions of student misconduct. Notably, there was a significant negative association between teacher perceptions of school crime and hallway territoriality (i.e. teachers perceived less crime in areas with signs of ownership such as trophy cases or murals).

#### Territoriality and undefined space

CPTED strategies often address undefined space^33^ that include semi-public areas without clear ownership, “that may not be seen as anyone’s responsibility to monitor or maintain (Astor, Meyer, & Pitner, 2001).” Astor et al. (2001) used mapping and individual interviews to identify areas that elementary and middle school students perceived as unsafe. Often, these areas had characteristics of undefined space, with a lack of adult supervision and overcrowding. Astor et al. (2001) recommended additional monitoring strategies: for example, having teachers stand in their classroom doorways and greet students in the hall during transition times. Hallway supervision by staff (other than security guards) was the only security measure that effectively reduced any form of peer victimization (compared to student ID badge requirements, cameras, security guards, or a formal student code of conduct) (Blosnich & Bossarte, 2011).

#### Implementation facilitation

Facilitation is an implementation strategy based on the Integrated-Promoting Action on Research Implementation in Health Services Framework (iPARiHS) (Harvey & Kitson, 2016; Kilbourne et al., 2013; Ritchie et al., 2014) that promotes provider self-efficacy (Bandura, 1977) in mitigating organizational barriers to EBI adoption (see Fig. 3). Facilitators are individuals who are familiar with the EBIs and organization’s procedures, climate, and processes with devoted time to support implementation activities; Facilitation includes diverse, implementation-science informed, tailored activities that enhance EBI delivery (e.g., stakeholder engagement) and identify and solve implementation challenges (Ritchie et al., 2014). Facilitation will be delivered via regular contact with the school staff and other 3-PLT members by the CS trained in program implementation and use of RJ, MHFA and CPTED in schools. The CS will support the school staff and 3-PLT in strategic thinking and program specific skills to address barriers related to the context, innovation, provider and recipients (see Fig. 3).

**Fig. 3 Fig3:**
[figure not shown]
Implementation facilitation guided by the iPARHIS framework (Harvey & Kitson, 2016), adapted

Although the 3-component intervention approach is consistent across schools, approaches to integrating the EBIs will be tailored, making complete standardization neither feasible nor desirable. The proposed study will include development of an implementation guide as part of the Facilitation implementation strategy. The implementation guide will provide scaffolding for the CS to work with the other 3-PLT members and school staff to integrate the interventions into each school setting. The guide will provide specific steps in delivering the EBIs across sites, but will allow for tailoring of the interventions (innovations) to meet the needs of the schools (context), their staff (providers) and their students (recipients) (Bonell et al., 2010; Patton, Bond, Butler, & Glover, 2003; Toumbourou et al., 2007); we therefore seek to evaluate district-wide (yet individualized) implementation of the three school safety components.

The CS, in collaboration with the 3-PLT will be provided with a comprehensive set of resources and training for components of MHFA, RJ, and CPTED. The 3-PLT will be trained to deliver MHFA training to all school staff, deliver restorative justice efforts (e.g., be trained in peer mediation and similar restorative processes and facilitate this within schools), and liaise with expert consultants of environmental design. Environmental design components will be tailored for each school’s unique physical and social structures; in general, aspects of the school’s image/management, and increasing ownership of undefined spaces will be emphasized. The CS will coordinate activities and efforts between the 3-PLT, school staff, parents and youth. The CS will also develop processes based on local evidence. These processes will aid in informing refinements to the implementation guide that will support program fidelity while guiding customization of adaptable elements, and long-term sustainability.

### Measures

A summary of the measures is provided in Table 2.

**Table 2 Tab2:** Data sources and measures

Aim	Measures	Measure frequency	Data Sources	Original Data Sources
Primary: Intervention effectiveness on violence outcomes	Aggression, violence victimization, bullying	Fall Year 1, Spring Year 1, Fall Year 2, Spring Year 2	Michigan Profile for Healthy Youth Survey (MiPHY)^a^	Youth Risk Behavior Surveillance Survey (YRBSS)^b^ Bully-Free Schools Survey (BFSS)^c^
	Truancy, behavioral referrals	Spring Year 1, Fall Year 2, Spring Year 2	School Information System (SIS)	School Student Data
Secondary: feasibility and potential utility of implementation facilitation	Meeting agenda, interview prompts	Spring Year 1, Spring Year 2	Staff, student and 3-Person Leadership Team (3-PLT) focus groups	Questions developed by research team
	School climate, perceptions of program effectiveness (e.g., violence)	Spring Year 1, Spring Year 2	Delaware School Climate Teacher/Staff Survey^d^	Delaware School Survey - Teacher/Staff (DSS-T/S)^d^
Secondary: mechanisms and mental health	School climate scale	Fall Year 1, Spring Year 1, Fall Year 2, Spring Year 2	Delaware School Climate Student Survey^d^	Delaware School Survey - Student (DSS-S)^d^
	Anxiety, depressive symptoms, wellbeing	Fall Year 1, Spring Year 1, Fall Year 2, Spring Year 2	Michigan Profile for Healthy Youth Survey (MiPHY)^a^	Youth Risk Behavior Surveillance Survey (YRBSS)^b^
Secondary: Cost-benefit	Intervention (e.g.,materials) and imple-mentation costs (e.g., training, support)	Monthly	Time tracking by research and school staff	Data collected by research team

^a^(Michigan Department of Education, 2016), ^b^ (Kann et al., 2018), ^c^ (Lindenberger, 2005), ^d^ (Bear et al., 2016)

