#### School-level discipline

The School Information System (SIS) is a web-based information system, implemented in GISD schools along with PBIS. It is designed to be an efficient, reliable, and confidential tool for collecting, summarizing, and using student discipline data, enabling school personnel to be more successful decision makers. Presently, schools in Genesee Co. report student violations and truancy via SIS, creating a standardized and comparable metric across schools in the proposed study area. We will compare treatment versus control school outcomes utilizing these data. Additional time will be allocated for more intensive analyses and linkage with MiPHY and focus group results.

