### Analysis

Our primary hypothesis is that students in schools receiving the intervention will report less violence (over time) compared to students in the control group. We also hypothesize that the intervention schools have an overall lower rate of violence over the school year compared with control schools. We expect that using implementation facilitation led by a climate specialist as part of a 3-person leadership team is a feasible and sustainable approach to integrating and effectively delivering the three intervention components. Finally, we expect that students in the intervention schools will report more positive school climate compared with those in control schools and that this, in turn, will result in lower improved mental health outcomes.

A cluster randomization design is proposed with random assignment by school to one of two arms: intervention or control. Evaluation of effectiveness outcomes will involve testing at four time points: a fall of Year 1, spring of Year 1, fall of Year 2, spring of Year 2. Measures will include school records and self-report data from students and teachers. The survey of students makes use of currently collected MiPHY data. Ten schools will be recruited in the first year and 10 in the following year; staggered recruitment will allow some initial evaluation testing of the program and allow the earliest possible start time with a number of schools. Including 20 schools in the research provides an opportunity to examine school level differences. To adjust for bias introduced by multiple comparisons across our outcome variables, we will use a pair of conservative (Tukey and Bonferonni) *p*-value adjustments in addition to reporting direct effect sizes (e.g., group differences in means) to allow for assessment not dependent on standard null hypothesis testing.

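### Table 2 gives the primary school-record outcomes no pre-intervention wave, conflicting with the four time points in the Analysis section and giving up cheap precision with 10 schools per arm

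*Protocol article*

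**What the plan says.** All references are to the protocol article.

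- **Status.** Table 2 lists "Truancy, behavioral referrals" under the primary aim, with SIS as the source. The School-level discipline subsection falls under Primary outcomes.
- **Schedule.** The SIS row reads "Spring Year 1, Fall Year 2, Spring Year 2". The student survey (MiPHY) rows and the student climate row read "Fall Year 1, Spring Year 1, Fall Year 2, Spring Year 2".
- **Analysis section.** "Evaluation of effectiveness outcomes will involve testing at four time points: a fall of Year 1, spring of Year 1", followed by fall and spring of Year 2. The next sentence names school records, with student and teacher self-report, as measures.
- **Data already held.** School-level discipline states: "Presently, schools in Genesee Co. report student violations and truancy via SIS". On the comparison it says: "We will compare treatment versus control school outcomes utilizing these data". It mentions no baseline.
- **Schools.** Ten schools per arm, 5 + 5 in each of two cohorts. The Schools subsection says: "Schools participating will be similar in terms of proportion of students receiving free/reduced school lunches".

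**The concern.** Two statements about a primary outcome do not agree. The Analysis section, read literally, gives school records a fall Year 1 point; Table 2 does not. A data manager working from Table 2 would request no pre-intervention SIS data.

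If Table 2 is followed, the SIS comparison sets 10 schools against 10 on post-start rates alone. A school's own earlier rate is then unavailable, both to reduce residual variance and to correct an unlucky allocation. With 20 clusters this matters more than in a trial with many units, and the data come from a system that is already running. Leaving the wave out of the schedule is also not a detail that an analysis plan can repair, because no model can adjust for data that were never extracted.

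**Working it through.** **1. The schedules side by side**

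| Source | Fall Y1 | Spring Y1 | Fall Y2 | Spring Y2 |
|---|---|---|---|---|
| Table 2, student survey and student climate | yes | yes | yes | yes |
| Table 2, SIS | no | yes | yes | yes |
| Analysis section, effectiveness outcomes | yes | yes | yes | yes |

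I read the years as each cohort's own intervention years, as the Data linking subsection does. A Spring Year 1 extract might cover the whole school year, but that year is an intervention year and so is not a baseline.

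**2. The plan's own figure.** There is none for the precision of the SIS comparison. The *d* = .27 in the power section is for 60 students per school at an intraclass correlation (ICC) of .10 and is not used here.

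**3. Precision gained from a baseline.** Let *r* be the school-level correlation between pre-intervention and follow-up rates. It is not in the article, so every value below is an assumption. Adjustment multiplies the residual variance by 1 − *r*², so the standard error falls by 1 − √(1 − *r*²). The equivalent number of schools is 20/(1 − *r*²). The detectable difference is in school-level SDs, from a noncentral *t* with 10 v 10 schools and 80% power. It assumes two-sided .05, because no alpha is stated for the between-group calculation. Degrees of freedom are 18 unadjusted and 17 adjusted.

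| *r* (assumed) | 1 − *r*² | SE reduction | Equivalent schools | Detectable difference |
|---|---|---|---|---|
| no baseline | 1.00 | – | 20 | 1.325 |
| .3 | .91 | 1 − .954 = 5% | 22 | 1.27 |
| .5 | .75 | 1 − .866 = 13% | 27 | 1.15 |
| .6 | .64 | 1 − .800 = 20% | 31 | 1.06 |
| .8 | .36 | 1 − .600 = 40% | 56 | 0.80 |

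**4. Is there between-school variance to remove?** The power section reports ICCs of .00 to .03 for the outcome measures. The between-school share of the variance of a school mean is ICC / [ICC + (1 − ICC)/m].

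- ICC .03, m = 60: .03/(.03 + .97/60) = .03/.0462 = 65%.
- ICC .03, m = 180: .03/(.03 + .97/180) = .03/.0354 = 85%.
- ICC .00: 0%.

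A small student-level ICC therefore does not rule out a worthwhile gain for school-level rates. At the bottom of the range there is none.

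**5. Chance imbalance.** With 10 per arm, the difference in arm means of any school characteristic has SD = √(2/10) = .447 school SDs. From Table 1, free/reduced lunch has mean 76.4, SD 14.3 and range 52–97, so the arm difference has SD 14.3 × .447 = 6.4 points. Permuting the 20 schools 10 v 10 (ignoring cohort), the arms differ by more than half an SD in about 27% of allocations. An imbalance of 0.5 SD in the earlier rate would shift the expected follow-up difference by 0.5*r* SDs: .15 at *r* = .3, .30 at .6 and .40 at .8.

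**The case against.** The strongest objection is that the Analysis section may mean a fall Year 1 SIS point is planned, so that Table 2 merely dropped an entry. That is possible. The four-time-point sentence is also loosely worded: it is followed by a mention of teacher self-report, which Table 2 schedules only each spring. It therefore cannot be read as a firm commitment to four SIS waves. A reader might infer that the trial is certainly post-only for these outcomes, and the article does not establish that. It does establish a conflict, and either resolution needs an edit.

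Three other tempting inferences also go too far:

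- **Bias.** Schools are randomized, so a comparison without a baseline is valid in expectation. The loss is in precision and in protection against an unlucky allocation.
- **The change analyses become impossible.** The subsections on dichotomous and quantitative variates do analyse change from baseline, but neither names truancy or referrals. The primary strategy, mixed-effects models on all available data, can be fitted to three waves.
- **Table 1 refutes the similarity claim across the board.** That claim covers only lunch eligibility and approximate size. Table 1 gives no school size, and its proficiency and minority columns do not bear on the claim. Only the lunch range does. All 20 schools meet the 50% eligibility threshold.

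It is also fair to say that the article reports no between-school variance for SIS rates and does not say that all 20 schools hold comparable prior-year data. The details of the SIS model may properly be left to an analysis plan.

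**Conclusion.** The point stands as an inconsistency in the schedule of a primary outcome, with an avoidable loss of precision if Table 2 is followed. It does not threaten the validity of the trial. The table omission and the conflict with the Analysis section can be read directly from the text. The size of the loss cannot: it rests wholly on an assumed correlation, with a standard-error reduction of about 5% at .3, 20% at .6 and 40% at .8. A reader might take the upper end as the expected gain, but nothing in the article supports choosing it. The change is worth making because the likely cost is small across the whole range.

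The statement that schools are similar on free/reduced lunch is a separate and minor wording point. It sits poorly with a 52–97% range.

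**What to change.** 1. Reconcile the SIS row of Table 2 with the Analysis section, stating how many SIS waves there are and what period each extract covers.
2. Add to the SIS row a retrospective extract of the school year before each cohort starts, where schools hold it. Fall Year 1 serves as a baseline only if it precedes the start of the intervention.
3. State that the SIS comparison is adjusted for the school's pre-intervention rate and for cohort.
4. Reword the similarity statement to match Table 1, for example by giving the lunch range and the 50% threshold.

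The cost is one more extract from an existing system, with whatever data-holder effort and approval that needs (the article does not say), plus a table edit. The model loses one degree of freedom for the earlier rate and one more for cohort, from 18 to 16.
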